**Fig. 1 Fig1:**
[figure not shown]
Overview of the study design

### Secondary objectives

The secondary goals of this study are.

1) to test the efficacy of the FACE self-help app in improving self-efficacy for managing emotions and problem-solving as facets of self- and emotion regulation, fear of negative evaluation and social avoidance as facets of social skills and social information processing, as well as self-esteem (secondary outcomes).

2) to test the differential effects of the self- and emotion regulation (SER) and the social skills and social information processing (SSIP) components on all outcomes. We hypothesize that SER will specifically improve self-efficacy for managing emotions and problem-solving and thus will have a greater effect on these variables than will SSIP. Similarly, we expect that SSIP will specifically improve fear of negative evaluation and social avoidance and thus will have a greater effect on these variables than will SER.

3) We aim to analyse the effects of the FACE self-help app on real-life ecological momentary assessment data in affective states, distress in several areas of life, social interactions, the use of coping strategies and resilience. We expect that the FACE self-help app will improve these variables compared to the waiting list control group.

4) Finally, we assess the degree of satisfaction of the participants with the FACE self-help app.

### Exploratory objectives

In exploratory analyses, we will examine whether improvements in self-efficacy for managing emotions, problem-solving, or self-esteem are mediators of resilience and well-being outcomes. Furthermore, we test whether the sequence of the components affects the outcomes. Adaptive emotion regulation may promote learning from social interactions, as well as foster social flexibility and effective adaptation to different social environments, as intensive negative emotions may impede its use in distressing situations. Thus, the sequence of SER and SSIP might lead to better outcomes than the sequence of SSIP SER. Finally, we will investigate whether possible effects of the intervention are moderated e.g. by the number, type, or the severity of ACE.

### Trial design

The study is conceptualized as a single-centre randomized controlled trial comparing an active intervention group against a waiting list control group (see Fig. 1). The intervention consists of two components (SER and SSIP) which are further compared in a crossover design to examine the differential effects of the components. The allocation ratio of the number of participants in the control group to the number of participants in the intervention group is 1:2. Randomisation is performed using a computer-generated allocation sequence.

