**Methods:**

The efficacy of the app will be tested through a single-centre, two-arm randomized controlled trial, comparing an active intervention group against a waiting list control group. The active group is divided into two subgroups, in which the two components are delivered in a different order to investigate differential effects in a crossover design. Up to 250 emerging adults aged 18 to 25 years with a history of ACE from a general population cohort study will be recruited. The primary objective is to test the efficacy of the app in improving resilience (primary outcome) and well-being (co-primary outcome) compared to a waiting list control group and to examine the stability of these effects. The secondary objectives include testing the efficacy of the app in improving the secondary outcomes, i.e., self-efficacy in managing emotions, problem solving, fear of evaluation, social avoidance, and self-esteem; examining the differential effects of the two components; and assessing the effect of the app on real-life data on resilience, affective states, distress in social interactions and coping strategies. Furthermore, the study will investigate potential moderators (e.g. ACE severity) and mediators of intervention outcomes (e.g. self-efficacy in managing emotions).

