## Methods

### Objectives

The primary objective is to test the efficacy of the FACE self-help app in improving resilience (primary outcome) and well-being (co-primary outcome) in emerging adults with a history of ACE compared to a waiting list control group (see Fig. 1). Then we aim to test the stability of the effects across three months in the intervention group. We hypothesize that the intervention group will significantly improve in all outcomes compared to the waiting list control group and that these outcomes will be stable.

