### Measures

#### Primary and secondary outcomes

All primary and secondary outcomes will be measured via online self-report questionnaires. Participants will be asked to complete them before the intervention (t0), 5 weeks after starting the intervention (t1, intermediate measurement), which will correspond to the time needed to complete the first component, and 11 weeks after starting the intervention (t2). By this time, participants will have completed both components of the intervention, which corresponds to the post-measurement. Furthermore, participants will be asked to complete the questionnaire again 11 weeks after finishing the FACE self-help app, which serves as a follow-up (t4). An exception is the adapted Patient Satisfaction Questionnaire, which will be assessed only after the finishing first component (t1), and after finishing the second component of the self-help app (t2). Reminders to fill out the questionnaire will be sent after 2 and 4 weeks.

***Resilience*** will be assessed with the 10-item German version [51] of the Connor-Davidson Resilience Scale (CD-RISC) [21], which has been shown to be a valid and reliable measurement [51, 52]. The CD-RISC is widely used and has been shown to be sensitive to change following interventions [21, 53]. The items are rated on a 5-point scale ranging from 0– Not true at all to 4– True nearly all the time.

***Well-being*** will be assessed with the Warwick-Edinburgh Mental Well-being Scale (WEMWBS) [54]. The German version of the scale shows good reliability and validity [55]. The scale contains 14 items that are rated on a 5-point scale ranging from 1– never to 4– always.

***Self-efficacy for managing emotions*** will be assessed with the PROMIS Short Form v1.0 - Self-Efficacy for Managing Emotions [56]. PROMIS items were developed for use in the general population for different aspects of mental health. Method and assessment timepoint: The scale contains 7 items that are rated on a 5-point scale ranging from 1– never to 4– always.

***Fear of negative evaluation*** will be assessed with the German short version of the Fear of Negative Evaluation Scale (SANB-5) [57]. The scale contains 5 items that are rated on a 4-point Likert scale from 1 - almost never true to 4- almost always true.

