### Statistical analyses

Analyses will be conducted according to the intention-to-treat paradigm. Additionally, we will conduct per-protocol analyses, including participants who complete baseline and post-intervention assessments and log into at least four modules defined as minimal therapeutic exposure. The significance level will be two-sided at *p* ≤ 0.05. To test the efficacy of the intervention in the intervention group compared to the control group, we will use linear mixed models. The differential effects of the SER and SSIP components will then be tested with interactions between the component and time. These analyses will model random slopes and intercepts for participants, test the fixed effects of the condition, as well as repeated assessments over time, using data from all participants. Linear mixed models have the advantage that they can account for missing values through maximum likelihood estimation [74]. Cohen’s d and f will be calculated as effect sizes. Furthermore, we will calculate Reliable Change Indexes [75].

Potential predictors and moderators of intervention outcome, such as gender or ACE severity will be analysed using multiple linear regressions. To analyse the mediation hypotheses and the longitudinal interplay of the variables, we will conduct path and structural equation analyses. Analyses will be conducted in SPSS, R and Mplus. There are no statistical stopping rules in this trial.

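### The SER versus SSIP contrast rests on unverified carry-over assumptions wherever it uses t2; the comparison of the two orders at t1 does not

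*Protocol article*

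**What the plan says.** All references are to the protocol article.

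- **Trial design:** the two components are ones "which are further compared in a crossover design to examine the differential effects of the components". The abstract's methods paragraph explains how: "The active group is divided into two subgroups, in which the two components are delivered in a different order".
- **Primary and secondary outcomes:** the first post-baseline assessment comes "5 weeks after starting the intervention (t1, intermediate measurement), which will correspond to the time needed to complete the first component". At t2, 11 weeks after the start, "participants will have completed both components of the intervention, which corresponds to the post-measurement". No washout between the components is described.
- **Objectives:** the hypothesis is that "the intervention group will significantly improve in all outcomes compared to the waiting list control group and that these outcomes will be stable". Stability is to be examined over three months.
- **Secondary objectives, item 2:** SER is expected to do more for managing emotions and problem-solving, and SSIP more for fear of negative evaluation and social avoidance.
- **Exploratory objectives:** "the sequence of SER and SSIP might lead to better outcomes than the sequence of SSIP SER". The reason offered is that better emotion regulation may help people learn from social situations.
- **Statistical analyses:** "The differential effects of the SER and SSIP components will then be tested with interactions between the component and time". The model has random intercepts and slopes and uses the repeated assessments. The test is not limited to the first period.
- **Sample size calculations:** three measurements, r = 0.6, and f = 0.10 for SER against SSIP, giving 162. The target is up to 250.

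**The concern.** A crossover contrast of outcome levels recovers the component difference only if the first component's effect has gone by the end of the second period, or carries over equally in both orders. The stability hypothesis contradicts the first condition. The second fails whenever lasting SER and SSIP effects differ, which is what secondary objective 2 proposes. A benefit of having SER first would add a further imbalance.

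By t2 everyone in the active arm has had both components. A difference between the orders at t2 therefore reflects order and carry-over as well as what each component does. At stake are the component-specific hypotheses. The same data could show about no difference, half of it, all of it, or more than all of it, depending on how the second period enters the model.

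**Working it through.** **Step 1. The plan's own figures.** For a within-between interaction, λ = f²·N·m/(1−r), with df (k−1)(m−1) and (N−k)(m−1).

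- f = 0.25, k = 2, m = 3, r = 0.6, N = 24: λ = 0.0625×24×3/0.4 = 11.25, power 0.835. The stated 24 reproduces.
- f = 0.10, k = 3, m = 3, r = 0.6, N = 162: λ = 0.01×162×3/0.4 = 12.15, power 0.801. The stated 162 reproduces.

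The arithmetic is sound. It also shows that t2 is one of the three measurements in the model that was sized.

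**Step 2. Expected scores.** Let a and b be the SER and SSIP effects on one outcome, L the share of the first component's effect that remains at t2, and g the extra gain at t2 from having SER first.

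- SER first: 0 at t0, a at t1, La + b + g at t2.
- SSIP first: 0 at t0, b at t1, Lb + a at t2.

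The contrasts for SER minus SSIP are then:

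- t1 only: a − b, whatever L and g are.
- Levels, by component just received: (a−b)(1−L/2) − g/2.
- Period changes (t0 to t1 against t1 to t2): (a−b)(1+(1−L)/2) − g/2.

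**Step 3. Numbers.** The article gives no component effects in SD. For illustration, the targeted component has 0.4 SD and the other 0.2 SD, a true difference of 0.20 in favour of the targeted component.

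| L | g | t1 only | Levels, SER-targeted | Levels, SSIP-targeted | Changes, SER-targeted | Changes, SSIP-targeted |
|---|---|---|---|---|---|---|
| 0 | 0 | 0.20 | 0.20 | 0.20 | 0.30 | 0.30 |
| 0.5 | 0 | 0.20 | 0.15 | 0.15 | 0.25 | 0.25 |
| 1 | 0 | 0.20 | 0.10 | 0.10 | 0.20 | 0.20 |
| 1 | 0.1 | 0.20 | 0.05 | 0.15 | 0.15 | 0.25 |
| 1 | 0.2 | 0.20 | 0.00 | 0.20 | 0.10 | 0.30 |

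**Step 4. Order by linear time.** With L = 1 and g = 0, the orders differ by 0, 0.20 and 0 at weeks 0, 5 and 11. Centred times are −5.33, −0.33 and 5.67, with sum of squares 60.67. The slope difference over 11 weeks is 11×(−0.33×0.20)/60.67 = −0.01. With categorical time, the t1 contrast stays at 0.20.

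**Step 5. Power with 83 per order** (250×2/3 ≈ 167 active, equal split assumed; r = 0.6; 4,000 simulated trials; g = 0; true difference 0.20 SD).

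| L | Levels | Changes | t1, baseline-adjusted |
|---|---|---|---|
| 0 | 0.82 | 0.70 | 0.36 |
| 0.5 | 0.59 | 0.55 | 0.36 |
| 1 | 0.30 | 0.38 | 0.36 |

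The second period's large gain in power appears only if effects vanish, which the plan does not expect. At L = 1 it is worth almost nothing.

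**Step 6. Power at t1 only.**

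- On the plan's scale (2 groups × 2 times, f = 0.10, r = 0.6), 166 active gives λ = 0.01×166×2/0.4 = 8.3 and power 0.82. N = 162 leaves 162×2/3 = 108 active, λ = 5.4 and power 0.63. Power of 0.80 needs 160 active.
- For 0.20 SD by ANCOVA, the residual SD is √(1−0.36) = 0.8 and the standard error 0.8×√(2/83) = 0.124. Power is 0.36. The detectable difference at power 0.80 is 0.35 SD, and 0.20 SD would need 252 per order.
- The two results differ because in a 2 × 2 layout f is a quarter of the difference in change, so f = 0.10 means 4×0.10 = 0.40 SD.

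**The case against.** The strongest reply is that the article never says the two periods will be pooled. The sample size of 162 reproduces with three groups at three times, which fits SER first, SSIP first and waiting list as parallel arms. On that view the word crossover may only describe the reversed order. With categorical time such a model contains the t1 contrast, undistorted. The coding of component and time, and any carry-over term, are details that a condensed article may leave to the analysis plan.

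Much of this stands. The missing coding is not held against the article. What remains is a conflict between things it does state: a crossover comparison, lasting effects, both components received by t2, and a test over the repeated assessments. Nothing stated makes the first period the test.

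Two stronger readings are tempting. A reader might infer that second-period data always pull the component contrast toward zero. The algebra does not support that. Period changes are undistorted under full persistence with no order gain, and too large under partial persistence. An order gain moves SER-targeted and SSIP-targeted outcomes in opposite directions. A reader might also infer that the plan predicts an order effect. It says only that SER first might do better, and treats this as exploratory.

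The stability hypothesis concerns the intervention group's outcomes over three months. Applying it to a single component over the six weeks from t1 to t2 (11 − 5) is a reasonable inference, not something the article states.

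**Conclusion.** The point holds in conditional form: a component contrast that uses t2 is interpretable only under carry-over assumptions that the trial does not verify and that partly conflict with its own hypotheses.

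Under full persistence and no order gain, a levels contrast shows half the true difference, an order-by-linear-time slope about none, and a period-change contrast all of it. Leaving aside chance cancellation, the period-change contrast is correct only under those two conditions. Any order gain g shifts SER minus SSIP by −g/2, against SER-targeted outcomes and in favour of SSIP-targeted ones.

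The halving is algebra. The SD values, g and the simulated powers rest on assumed effects, an equal split of the active arm and no dropout. The t1 contrast also relies on the division into the two orders being randomised. The primary comparison of the active arm with the waiting list is not affected, and the stated sample sizes are not in error.

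**What to change.** State that secondary objective 2 is tested by the baseline-adjusted difference between SER-first and SSIP-first at t1, with participants analysed in the order to which they were randomised. Use t2 only for the exploratory comparison of the two orders. Label any estimate that combines both periods as descriptive, and give its assumptions about persistence and order.

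The t1 data are already collected, so this changes the wording of one analysis. The cost is the second period's nominal precision. The lower t1-only power should be stated openly: adequate before dropout for f = 0.10 if about 167 active participants are randomised, short of 0.80 if recruitment stops at 162 in all, and low for a difference near 0.20 SD.

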### Participants and procedures

Participants will be recruited between August 2023 and July 2024 from the FACE epidemiological study sample, which is based on a random list-based general population sample of emerging adults aged 18–21 at baseline in German-speaking Switzerland. This part of the study was described in detail in an earlier study protocol [50]. The FACE epidemiological study assesses different types of ACE, i.e., emotional abuse and neglect, physical abuse and neglect, sexual abuse, witnessing domestic violence, household dysfunctions but also peer verbal, physical and sexual abuse.

Emerging adults who reported a history of ACE in the FACE epidemiological study will be invited to participants in the self-help app evaluation study via an e-mail from the study collaborators. The e-mail invitation contains a written study information regarding the procedure and study content as well as a link to schedule an appointment for the interview. In the interview, the suitability of the self-help app for the situation of the respective emerging adult will be discussed and, in case of an acute crisis, participants will be informed about support and health-care services such as psychiatric outpatient clinics. After sending back the signed written informed consent to the study team, participants will receive the online questionnaires.

The inclusion criteria are (1) self-reported ACE; (2) written informed consent; (3) the possession of a smartphone; (4) mastery of the German language; (5) an age between 18 and 25 years. The exclusion criteria are (1) acute suicidality and (2) the inability to follow the procedures of the study, e.g. due to comprehension problems, visual impairment, lack of sufficient motor skills, or severe psychological or somatic disorders that require immediate treatment that impedes continuous work on the self-help program. These points will be discussed with the participants during the screening procedures.

### Measures

#### Primary and secondary outcomes

All primary and secondary outcomes will be measured via online self-report questionnaires. Participants will be asked to complete them before the intervention (t0), 5 weeks after starting the intervention (t1, intermediate measurement), which will correspond to the time needed to complete the first component, and 11 weeks after starting the intervention (t2). By this time, participants will have completed both components of the intervention, which corresponds to the post-measurement. Furthermore, participants will be asked to complete the questionnaire again 11 weeks after finishing the FACE self-help app, which serves as a follow-up (t4). An exception is the adapted Patient Satisfaction Questionnaire, which will be assessed only after the finishing first component (t1), and after finishing the second component of the self-help app (t2). Reminders to fill out the questionnaire will be sent after 2 and 4 weeks.

***Resilience*** will be assessed with the 10-item German version [51] of the Connor-Davidson Resilience Scale (CD-RISC) [21], which has been shown to be a valid and reliable measurement [51, 52]. The CD-RISC is widely used and has been shown to be sensitive to change following interventions [21, 53]. The items are rated on a 5-point scale ranging from 0– Not true at all to 4– True nearly all the time.

***Well-being*** will be assessed with the Warwick-Edinburgh Mental Well-being Scale (WEMWBS) [54]. The German version of the scale shows good reliability and validity [55]. The scale contains 14 items that are rated on a 5-point scale ranging from 1– never to 4– always.

***Self-efficacy for managing emotions*** will be assessed with the PROMIS Short Form v1.0 - Self-Efficacy for Managing Emotions [56]. PROMIS items were developed for use in the general population for different aspects of mental health. Method and assessment timepoint: The scale contains 7 items that are rated on a 5-point scale ranging from 1– never to 4– always.

***Fear of negative evaluation*** will be assessed with the German short version of the Fear of Negative Evaluation Scale (SANB-5) [57]. The scale contains 5 items that are rated on a 4-point Likert scale from 1 - almost never true to 4- almost always true.

***Social avoidance*** will be assessed with the subscale social-behavioural avoidance from the German version of the cognitive-behavioural avoidance scale (KBVS) [58]. The subscale contains 8 items that are rated on a 5-point Likert scale from 1 - not at all applicable for me to 5 - absolutely applicable for me.

***Problem-solving*** will be assessed with German version [59] of the short form of the Social Problem-Solving Inventory-Revised (SPSI-R) [60]. The scale contains 25 items that are rated on a 5-point scale from 0– not at all true to 4– extremely true.

***Self-esteem*** will be assessed with the German version [61] of the Rosenberg Self-Esteem Scale [62]. The scale contains 10 items that are rated on a 4-point scale from 1– not at all true to 4– extremely true.

***Acceptance*** of the intervention will be assessed with the Patient Satisfaction Questionnaire (ZUF-8), a self‐report measure that explores patients’ overall satisfaction with digital interventions [63]. It contains eight items that are rated on a 4‐point scale. The German version of the ZUF‐8 showed adequate psychometric properties with good internal consistency, construct validity, and concurrent validity [63].

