### Study intervention

The FACE app is based on a transdiagnostic model of mechanisms linking childhood trauma to psychopathology and addresses the thematic components Self- and Emotion Regulation (SER) and Social Skills and Social Information Processing (SSIP) for the promotion of resilience and well-being. It was developed based on well-established cognitive-behavioural principles that have been used in other web-based self-help apps [13] and offers psychoeducative materials and exercises in various formats (text, audio, video).

In addition to two components SER and SSIP (see Fig. 1), there are two additional parts intended to frame the user’s experience: an introduction and a conclusion/farewell. First, the general introduction, available to everyone from the start, explains the app interface, presents general information on ACE (psychoeducation about prevalence, types, and consequences), and encourages reflection on one’s personal status and resources plus the formulation of personal goals for the app. Towards the end of the intervention, the conclusion/farewell encourages the revisiting of the goals and ideas of the start and the reflection on what was most helpful while using the app. In addition, a collection of short activities and exercises relevant to everyday life and promoting physical and mental well-being is accessible as a toolbox at all times, but also referred to at relevant moments throughout the rest of the content.

Within each of the two thematic components SER and SSIP, four different modules include informational reading on ACE and ACE-related topics, as well as prompts for participants to actively reflect on what was learned in the readings and exercises to apply their knowledge and practice skills (see Table 1). The first module includes information about ACE in relationship with SER or SSIP respectively. Modules 2 and 3 contain information about the theoretical background of SER or SSIP respectively as well as information, writing tasks and exercises on the modification of possible cognitive biases. In module 4, the focus is on learning new skills and their implementation/transfer in daily life. Participants are encouraged to work through one module per week and to complete the exercises, which adds up to approximately one hour of engagement with the app per week.

**Table 1 Tab1:** Outline of the components of the FACE self-help app

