#### Participants’ support and guidance

During the 10 weeks of the use of the FACE self-help programme, participants will receive weekly written feedback and support via an integrated messenger function - either from a psychologist or social worker of the School of Social Work at the University of Applied Sciences and Arts Northwestern Switzerland or from trained and supervised master students in Clinical Psychology of the University of Bern. This weekly support, which was short but individualised in terms of progress and focus, acknowledges and motivates participants in their engagement with the app, keeping emphasis on positive reassurance. It aims to improve adherence, provides a weekly structure, support for technical problems and the possibility to ask further questions. If needed, stabilising interventions via phone calls are offered by a psychologist within the FACE team who can also, if needed, provide support with seeking more comprehensive treatment through counselling services, psychotherapists or psychiatrists close to where the participants live. Reports of adverse events and negative effects will be collected.

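### Reminders 2 and 4 weeks after t1 prompt late answers during the second component and can dilute the SER-versus-SSIP contrast (secondary objective 2)

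*Protocol article*

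**What the plan says.** All places are in the Methods of the protocol article unless stated.

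- **Timing of t1** (Primary and secondary outcomes): the questionnaire is due "5 weeks after starting the intervention (t1, intermediate measurement), which will correspond to the time needed to complete the first component". The post-intervention wave t2 is at week 11.
- **Reminders** (same section): "Reminders to fill out the questionnaire will be sent after 2 and 4 weeks". No exception is made for t1.
- **Pace** (Study intervention; Participants' support and guidance): each component has four modules, and "Participants are encouraged to work through one module per week". App use lasts 10 weeks in total.
- **EMA** (Ecological momentary assessments; Discussion): a one-week block follows the first component, and the Discussion places this block between the two components.
- **Component comparison** (Trial design; Statistical analyses): SER and SSIP are two components "which are further compared in a crossover design to examine the differential effects of the components". The analysis is stated as "The differential effects of the SER and SSIP components will then be tested with interactions between the component and time".
- **Hypothesis** (Secondary objectives): "SER will specifically improve self-efficacy for managing emotions and problem-solving", with the mirror-image expectation that SSIP acts on fear of negative evaluation and social avoidance.

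**The concern.** The two active sequences receive the same two components in opposite order. At t1 they have had different components. At t2 and at follow-up both have had both, and no washout is described. For the questionnaire scales named in secondary objective 2, t1 is therefore the wave that carries the contrast.

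The reminder rule works against this. A reminder two or four weeks after the t1 due date asks for the answer when the participant may already be working on the other component. If that answer is analysed as the week-5 value, it mixes some of the second component into a measurement meant to reflect the first alone. The same happens in the opposite direction in the other sequence, so the two move closer together. A null SER-versus-SSIP result would then be hard to interpret: it could mean equal effects or late measurement.

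**Working it through.** **1. The plan's own sample sizes.** For the within-between interaction in repeated measures, with N participants, k groups, m measurements and correlation ρ:

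λ = f² · N · m / (1 − ρ), df1 = (k − 1)(m − 1), df2 = (N − k)(m − 1).

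With ρ = 0.6, α = 0.05 and m = 3 (Sample size calculations):

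- f = 0.25, k = 2, N = 24: λ = 0.0625 × 24 × 3 / 0.4 = 11.25, power 0.835.
- f = 0.10, k = 3, N = 162: λ = 0.01 × 162 × 3 / 0.4 = 12.15, power 0.801.

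Both stated figures (24 and 162) reproduce, and this point does not change them.

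**2. When the reminders fall.** Counted from the t1 due date: 5 + 2 = week 7 and 5 + 4 = week 9. The starting point of the count is not stated; the due date is the natural reading.

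**3. Where the second component lies.** Ten weeks of use within 11 weeks leaves one week, which fits the EMA block between the components: 5 + 1 + 5 = 11. On this reading the second component runs from week 6 to week 11. An answer at week 7 comes 1/5 = 0.2 of the way through, and one at week 9 comes 3/5 = 0.6 of the way through.

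**4. Dilution (assumption: benefit accrues linearly, and late responders keep to the module schedule).** A person who has done a fraction q of the second component keeps (1 − q) of the SER-minus-SSIP contrast. With shares p7 and p9 answering at weeks 7 and 9:

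retained fraction = 1 − (0.2 · p7 + 0.6 · p9).

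The documents give no late-response rate, so p7 and p9 are assumed. For p7 = 0.20 and p9 = 0.15:

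1 − (0.04 + 0.09) = 0.87, a shrinkage of 13%, so f = 0.10 becomes 0.087.

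**5. Power for the contrast.** With 1:2 allocation and 250 randomised, 250 × 2/3 ≈ 167 people are in the active sequences, before dropout. Taking two sequences and two waves (t0, t1), so k = 2, m = 2, ρ = 0.6, df = (1, 165):

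| Late at week 7 / week 9 | Retained | f | λ | Power |
|---|---|---|---|---|
| 0% / 0% | 1.00 | 0.100 | 8.35 | 0.82 |
| 10% / 10% | 0.92 | 0.092 | 7.07 | 0.75 |
| 20% / 15% | 0.87 | 0.087 | 6.32 | 0.71 |

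The result depends on the assumed span of the second component. If it runs over weeks 5–11 (fractions 0.33 and 0.67), the 20%/15% case retains 0.833 and power is 0.67. If it runs over weeks 5–10 (0.40 and 0.80), it retains 0.80 and power is 0.63. If late responders have not opened the second component, q is 0 and nothing is lost.

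**6. Would excluding late answers help?** In the 20%/15% case, 167 × 0.65 ≈ 109 people remain. Then λ = 0.01 × 109 × 2 / 0.4 = 5.45 and power is 0.64, below the 0.71 with dilution. In the 10%/10% case, 134 remain and power is 0.73, against 0.75 with dilution.

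**The case against.** The strongest reply is that the loss is conditional. It needs a material share of late answers, a second component that is open to someone who has not answered t1, and actual work on it by that person. The article states none of these. It places t1 between the components, says that only the introduction is open to everyone from the start, and programs the questionnaires in the app, so holding the second component until t1 is answered would be technically possible. People who ignore a questionnaire for weeks may also have stopped using the modules. A further reply is that response windows and late-answer rules are commonly left to the full protocol or the SAP, and that late reminders protect against non-response, a limitation the authors name.

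Most of this stands. It means that dilution is a risk of unknown size, and that the lack of a stated closing date is not in itself a finding. What remains is the reminder rule: it is stated, makes no exception for t1, and asks for answers at times when the components have begun to cross.

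A reader might infer more than the documents support:

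- *That t1 is contaminated as a matter of fact.* Only late answers are exposed, and their share is unknown.
- *That no other clean measurement exists.* The t1 EMA block is tied to a fixed week with 30-minute prompt windows and covers affect, coping, burden, resilience and social interactions. It does not carry the scales named in the differential hypotheses, so it cannot replace the t1 questionnaire for them.
- *That late t2 answers from controls overlap with their access to the app.* The text does not say when controls get access, and the design figure is not shown.
- *That the mediation analyses are harmed.* They are exploratory, and the article does not say that they use t1.

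**Conclusion.** The point holds as a moderate weakness in the schedule. Followed as written, the reminder rule prompts t1 answers at about weeks 7 and 9, inside the second component for a participant on schedule, and such answers can bias the SER-versus-SSIP contrast toward no difference. Under the assumed late shares of 20% and 15%, a second component over weeks 6–11 and linear accrual, the contrast loses about 13% and power drops by about 11 percentage points, from 82% to 71%. The loss grows if the second component starts at week 5 and vanishes if late responders have not begun it.

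It would be tempting to read this as a threat to the trial's main result. The documents do not support that: the primary comparison of app with waiting list at t2 does not depend on t1 timing in this way, only secondary objective 2 is clearly exposed, and the error runs toward a missed difference, not a false one.

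**What to change.** - **Reminders.** For t1, send both reminders within days of the due date, during the t1 EMA week and before the second component opens. An equivalent route is to release the second component only once t1 is answered or its window has closed. If release already works this way, the article need only say so.
- **Dates.** Record the completion date of every questionnaire.
- **Analysis.** Keep late t1 answers in the main analysis. Pre-specify a sensitivity analysis of the component contrast that uses actual completion time or excludes late t1 answers. Exclusion should not be the main rule: on the figures above it costs at least as much power as the dilution, and it makes missingness selective, which a mixed model handles only under missing at random.

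The cost is a changed setting in the reminder schedule and a short addition to the analysis plan, with possibly a few more missing t1 values. If collection is already complete, the analysis part still applies wherever completion dates were stored.
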